## Selection of comparison groups/controls

Not applicable

## **Exposures, outcomes and covariates**

Exposure: record of intellectual disabilities

The exposure variable will be a record of intellectual disabilities. Patients with intellectual disabilities will be identified using searches for any code included in Appendix 1, as has been done previously with CPRD (Carey et al. 2016; 2017).

Primary outcome: challenging behaviours

Outcome variables will be presence of challenging behaviours, which will be identified by Read codes in Appendix 1 (Sheehan et al. 2015; ).

Moderator: record of co-occurring physical conditions

Patients with intellectual disabilities and co-occurring physical conditions (i.e. pain, sleep problems, constipation, epilepsy, urinary/bowel incontinence and sensory impairments) will be identified using searches for any relevant READ code, as has been done previously with CPRD (e.g. Glover et al. 2017; Hosking et al. 2016).

Mediators:

severity of intellectual disabilities, co-occurring autism/genetic syndromes/mental comorbidities will be identified using searches for any code included in Appendix 1 (e.g. Glover et al. 2017; Hosking et al. 2016; Houghton et al. 2018)

Confounding covariates:

Demographic (age, gender, ethnicity) and socioeconomic (Practice/Patient Level Index of Multiple Deprivation) factors

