## **Objectives, specific aims & rationale**

The aim of this project will be firstly to investigate longitudinal trends in the incidence of challenging behaviours in a nationwide population of primary care patients with intellectual disabilities, using data from the Clinical Practice Research Datalink. We will also investigate if there is an association between physical conditions and challenging behaviours in patients with intellectual disabilities and what the nature and direction of this association may be.

The project aims to answer the following research questions:

1. What is the 1-, 5- and 10-year incidence of challenging behaviours in a nationwide population of primary care patients with intellectual disabilities?
2. Do physical conditions (i.e. pain, sleep problems, constipation, epilepsy, urinary/bowel incontinence and sensory impairments) increase/decrease the incidence of challenging behaviours in primary care patients with intellectual disabilities?
3. To what extent do health factors (i.e. severity of intellectual disabilities, co-occurring autism/genetic syndromes/mental comorbidities) affect the incidence of challenging behaviours in primary care patients with intellectual disabilities?
4. Is the relationship between the presence of physical conditions and challenging behaviours in patients with intellectual disabilities accounted for by demographic (e.g. age, gender, ethnicity) and socioeconomic (e.g. Practice/Patient Level Index of Multiple Deprivation) factors?

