A more recent systematic review identified 38 studies investigating association of challenging behaviours with 11 behavioural, psychiatric and psychosocial factors (van den Akker et al. 2020), but association with physical conditions has been less investigated despite the fact that epidemiological studies show that patients with intellectual disabilities have more physical conditions than the general population (e.g. Cooper et al. 2015). A systematic review of studies investigating the association of physical conditions with challenging behaviours in population with intellectual disabilities identified 45 studies, which looked at general medical conditions, motor impairment, epilepsy, sensory impairment, gastrointestinal disease, sleep disorders, dementia and other conditions. Among the identified studies, there were only four high-quality and seven well-conducted observational studies. Significant and independent associations were found for challenging behaviours and urinary incontinence, pain related to cerebral palsy and chronic sleep problems, and between self-injurious behaviour and visual impairment. No association was found with hearing impairment, bowel incontinence, mobility impairment or epilepsy. Many other physical conditions were not addressed at all (de Winter et al. 2011).

Furthermore, contradicting findings on epilepsy were reported in a systematic review by Deb et al. (2020), who after sensitivity analysis, found a significantly higher rate of overall challenging behaviours in the epilepsy group compared with the non-epilepsy group in a meta-analysis of 10 studies, but the effect size was very small (0.16). Aggression and self-injurious behaviour both showed a statistically significant higher rate in the epilepsy group, with very small effect sizes (0.16 and 0.28 respectively). No significant intergroup difference was observed in the rate of stereotypy (Deb et al. 2020).

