## Definition of the study population

Data on all patients with intellectual disabilities will be acquired from CPRD. Individuals with intellectual disabilities will be identified using Read codes in Appendix 1. Co-occurring challenging behaviours will be defined as a binary variable (present or not) based on READ codes in Appendix 1. Patients registered in a practice between January 1 January 2009 and 31st December 2019 will be included in the study. We require that their practice allows linkage to HES, MHSDS and IMD data, resulting in the inclusion of English practices. Patients who are registered at CPRD practices not participating in the linkage scheme, or who have individually opted out, will not be included.

Earliest cohort entry date will be 1/1/2009. Patients who register after 1/1/2009, or who are diagnosed with intellectual disabilities during the study period, will be followed from that date. Patients will be censored if they transfer out from their CPRD practices, or opt out before the end of the study period (31/12/2019). However, challenging behaviour diagnoses of patients who leave a CPRD practice prior to the end of the study period will be included in a sensitivity analysis.

Index case for a case would be one of the following:

- 1/1/2009 (if a patient is actively registered on this date with a diagnosis of challenging behaviours prior to 2009)
- date of diagnosis (if a patient's date of first diagnosis of challenging behaviours is after 1/1/2009 while they are registered)
- date of registration (if a patient's date of registration is after 1/1/2009 and they have a prior diagnosis to that registration)

Inclusion criteria:

- all patients with intellectual disabilities (as defined in READ codes in Appendix 1) registered at a general practice for at least six months prior to cohort entry date
- patients who receive a diagnosis of intellectual disabilities after cohort entry date and have a valid registration status for at least six months

Exclusion criteria

- patients registered at practices not participating in the linkage scheme, or who have individually opted out

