## **Data/statistical analysis**

The analysis will be performed using STATA/SPSS Software. In our main analyses, patients will be stratified into subgroups by age, sex and co-occurring intellectual disabilities. All of the analyses as described below will be performed for each subgroup.

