### **Phase 2**

The main statistical analyses will be conducted using stratified Cox proportional hazard models (Sjolander & Greenland 2013). The Cox models will be run univariately, then multivariably. The multivariable analysis will comprise (i) adjustment for demographic (age, gender, ethnicity) and socioeconomic (Practice/Patient Level Index of Multiple Deprivation) factors, (ii) the addition of mediators (i.e. severity of intellectual disabilities, co-occurring autism/genetic syndromes/mental comorbidities) factors) to the above model to assess any attenuation in the associations (iii) the use of likelihood ratio tests to test for interaction effects with the effect modifier (i.e. physical conditions including pain, sleep problems, constipation, epilepsy, urinary/bowel incontinence and sensory impairments) if there is sufficient statistical power and if found to be statistically significant, further sub-group analyses. We will test for proportional hazards in the Cox models using both graphical methods and a formal statistical test based on Schoenfeld residuals. Where the assumption of proportional hazards is violated, we will augment the models with time varying covariates. To account for patients with multiple events over the 10-year study period and investigate incidence rate ratios, we will conduct a Poisson regression, similarly to the methodology applied by Sheehan et al. (2015).

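### The named exposure, intellectual disability, is present in every patient, and no listed model step specifies the adjusted main effect of the physical conditions that research questions 2 and 4 ask about

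*Protocol*

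**What the plan says.** All places are in the protocol.

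- **Exposure.** Exposures, outcomes and covariates: "The exposure variable will be a record of intellectual disabilities". The same section and Outcomes to be measured label the physical conditions a moderator.
- **Population.** Definition of the study population: "Data on all patients with intellectual disabilities will be acquired from CPRD". The first inclusion criterion is "all patients with intellectual disabilities (as defined in READ codes in Appendix 1) registered at a general practice for at least six months" before cohort entry; the second covers patients diagnosed later. Patients diagnosed during the study are followed from that date.
- **Comparator.** Selection of comparison groups/controls: "Not applicable".
- **Stratification.** Data/statistical analysis: "patients will be stratified into subgroups by age, sex and co-occurring intellectual disabilities", with every analysis repeated in each subgroup.
- **Question.** Research question 2: "Do physical conditions (i.e. pain, sleep problems, constipation, epilepsy, urinary/bowel incontinence and sensory impairments) increase/decrease the incidence of challenging behaviours"? Research question 4 asks whether that relationship is accounted for by demographic and socioeconomic factors. The same section also seeks the direction of the association.
- **Models.** Phase 2 runs Cox models univariately, without naming the covariate, and then multivariably. Step (i) adjusts for demographic factors and deprivation. Step (ii) adds the health factors called mediators and looks for attenuation. Step (iii) is "the use of likelihood ratio tests to test for interaction effects with the effect modifier", which is where the physical conditions are named, and it depends on sufficient power.
- **Stated intent.** The Technical Summary and the section on planned use of linked data both say that stratified Cox models will examine the association of challenging behaviours with physical conditions.
- **Descriptive use.** Phase 1 allows incidence to be stratified by physical conditions, among other factors, where cell sizes permit.

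**The concern.** The protocol gives two incompatible accounts of its exposure. The title, the objectives and the Technical Summary make it the physical conditions. The role definitions make it intellectual disability, with the physical conditions modifying its effect. The second account cannot be carried out in a cohort where everyone has intellectual disabilities.

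The estimate at stake is the central one: the adjusted hazard ratio for each physical condition. An analyst who follows the role definitions has no model to fit. One who departs from them must choose the exposure, its timing and the terms of the interaction test without guidance from the protocol, in a study whose type is given as hypothesis testing.

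**Working it through.** **1. The plan's own counts.** From Sample size considerations:

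- 3,020,680 + 13,285,111 = 16,305,791 registered patients.
- 16,305,791 × 0.005 = 81,528.96, stated as 81,529.
- 81,529 × 0.165 = 13,452.3, stated as 13,452.

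Both figures reproduce. They count patients with intellectual disabilities and, among them, those with challenging behaviours. Neither is a contrast between exposed and unexposed patients.

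**2. Information on the named exposure.** For a binary exposure with share p and d events, the Schoenfeld information on the log hazard ratio is d·p·(1 − p). Here p = 1. Even if all 13,452 were events, the information is 13,452 × 1 × 0 = 0.

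The partial likelihood shows the same. With x = 1 for everyone, each event contributes exp(β + γz_i) / Σ_j exp(β + γz_j), and exp(β) cancels. In a simulated Cox model with a constant covariate (n = 2,000), the log partial likelihood was −9020.327 at β = 0, 1 and 5, and the Hessian was 0. In the planned Poisson model the same variable would be collinear with the intercept.

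Late diagnosis does not create a contrast over time, because follow-up starts at diagnosis.

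**3. Effect modification and stratification.** If x = 1 for everyone, the product of x and condition c is c itself. An interaction of intellectual disability with a condition cannot be told apart from the main effect of that condition. Stratifying on x gives one stratum.

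**4. Where the physical conditions enter Phase 2.**

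| Step | Terms named | Physical conditions named? |
|---|---|---|
| Univariate Cox | None | Not stated |
| (i) | Age, gender, ethnicity, deprivation | No |
| (ii) | Adds severity, autism, genetic syndromes, mental comorbidities | No |
| (iii) | Likelihood ratio test of interaction | Yes, as effect modifier, if power allows |
| Poisson | None | Not stated |

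No row specifies an adjusted main effect of a physical condition, and step (iii) does not say which variable the conditions are crossed with.

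**5. What naming the conditions restores.** With a condition as exposure, 0 < p < 1 and a contrast exists. The protocol gives neither condition prevalences nor target hazard ratios, so both are assumed here, with two-sided α = 0.05 and 80% power. Events needed = (1.960 + 0.842)² / [p(1 − p)(ln HR)²].

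| Assumed prevalence p | Events, HR 1.2 | Events, HR 1.1 |
|---|---|---|
| 2% | 12,047 | 44,084 |
| 10% | 2,624 | 9,601 |
| 30% | 1,125 | 4,115 |

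The stated 13,452 is a prevalent count, so it cannot be read as the number of incident events available.

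**The case against.** The strongest reply is that this is mislabelling and the intended analysis is plain. The Technical Summary and the linked-data section say the Cox models will examine physical conditions. Research question 4 asks about the very factors that step (i) adjusts for, so the associations checked for attenuation are plausibly those of the conditions. Role labels are loose elsewhere: mental comorbidities are mediators in most places but a moderator in the linked-data section. The stratifier may be a slip for severity of intellectual disabilities, which Phase 1 uses. Much of this stands as evidence of intent. It does not supply the missing term, and it conflicts directly with the exposure that is named.

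Four stronger readings might be inferred, and the protocol does not support them.

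- **That research question 2 is never to be estimated, or that the conditions appear only in the interaction test.** Phase 1 may give incidence by condition, though descriptively, unadjusted and only where cells allow. The univariate Cox covariate is left open, and the intent to model the association is stated.
- **That the hazard ratios will be biased by a known amount.** Simulations with no true effect gave hazard ratios of 0.51 to 0.67 when a condition was coded as ever recorded up to event or censoring. The rates were assumed and the protocol does not state that coding. Baseline coding in the same simulations gave 0.92 to 1.01.
- **That the age and sex subgroups of the main analyses contradict the subgroup analyses in Phase 2.** The latter follow a significant interaction with physical conditions and can be a different set.
- **That incontinence and sensory impairment will be analysed as combined terms.** Study background reports an association for urinary incontinence but also says "No association was found with hearing impairment, bowel incontinence, mobility impairment or epilepsy". The combined wording is only a list label, however, and splitting the terms is a preference.

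**Conclusion.** The concern holds as a contradiction over the exposure together with an unspecified main effect. That the stated exposure is not estimable is exact: it follows from the eligibility rule and the absence of a comparator, and needs no assumed rates. That the adjusted effect of physical conditions is unspecified follows from reading the Phase 2 steps as listed. An unseen statistical analysis plan might add the term, but the protocol's definition of the exposure would still be wrong.

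Timing is a supporting point. The conditions are defined as co-occurring records with no order relative to the behaviour, while the questions concern incidence and direction. No magnitude for this can be taken from the protocol. The contradiction should be resolved before analysis.

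**What to change.** 1. Make intellectual disability the eligibility criterion. Delete it as exposure in Exposures, outcomes and covariates and as stratifier in Data/statistical analysis. Reconcile that stratifier with Phase 1, which uses severity of intellectual disabilities.
2. Name each physical condition as the exposure in Outcomes to be measured, in Exposures, outcomes and covariates, and in Phase 2. Report its hazard ratio univariately, then after step (i), then after step (ii).
3. State which variables step (iii) crosses with the conditions.
4. Date each condition at its first code and enter it as a time-updated covariate, so that only conditions recorded before the behaviour count as exposure.

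The cost is protocol wording, a split of person-time at the condition date and some extra analysis code. No additional data are needed.

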### **Phase 1**

We will calculate the incidence of challenging behaviours within the group with intellectual disabilities. Our binary outcome will be defined on the basis of having a record of a relevant Read code for co-occurring challenging behaviours (Appendix 1). Records will be stratified by age, sex, severity of intellectual disabilities and/or co-occurring physical conditions/autism/genetic syndromes/mental comorbidities if cell sizes allow. Tables of baseline characteristics will be described for all patients with intellectual disabilities. For continuous data, mean, median, range, and standard deviations will be calculated. For categorical variables, frequency and percentages will be reported.

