## **Plan for addressing confounding**

We plan to adjust for the following confounding factors: sex, age, ethnicity, socioeconomic status using the Practice/Patient Level Index of Multiple Deprivation.

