## Limitations of study design

Practice-based deprivation measure may not represent individual-level socioeconomic status. Information on the socioeconomic status of patients is available for English practices only, which may limit the generalisability of our findings. There may also be an under-representation of people with intellectual disabilities and co-occurring challenging behaviours in the dataset, as there may be a significant number of patients without a formal diagnosis. Errors and inconsistencies in recording challenging behaviours may present problems in data quality. There may also be unrecorded or unreported physical conditions in the population with intellectual disabilities in the primary care data. In investigating the association of specific physical conditions with challenging behaviours, we may be limited to analysing more common physical conditions only due to small sub-sample sizes. Variation in coding across different practices and over time may introduce systematic biases. Linkage to the HES Admitted Patient Care and Mental Health Services Data Set (MHSDS) may limit the sample size, depending on the quality of the linked data.

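### Outcome and physical conditions both come from recorded codes and no analysis allows for practice contact, so the hazard ratios may be biased, probably upward, by unequal recording

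*Protocol*

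**What the plan says.** Under Exposures, outcomes and covariates, the Protocol states: "Outcome variables will be presence of challenging behaviours, which will be identified by Read codes in Appendix 1". Phase 1 repeats this: "Our binary outcome will be defined on the basis of having a record of a relevant Read code for co-occurring challenging behaviours". No scheduled or independent assessment of behaviour is planned.

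The physical conditions come from the same kind of source. Patients who have them "will be identified using searches for any relevant READ code, as has been done previously with CPRD".

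On the models, Phase 2 says: "The main statistical analyses will be conducted using stratified Cox proportional hazard models". The first adjustment step covers demographic and deprivation factors, in line with the plan for confounding: "We plan to adjust for the following confounding factors: sex, age, ethnicity, socioeconomic status using the Practice/Patient Level Index of Multiple Deprivation". The second step is "the addition of mediators (i.e. severity of intellectual disabilities, co-occurring autism/genetic syndromes/mental comorbidities) factors) to the above model to assess any attenuation".

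The linkages have other purposes. The section on planned use of linked data assigns the hospital admissions data to interaction tests with physical conditions. It assigns the mental health services data to the role of mental comorbidities. Neither is assigned to finding the outcome.

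Two sensitivity analyses are named: one on diagnoses in patients who leave a practice (Definition of the study population) and one using multiple imputation (Plans for addressing missing data).

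Limitations of study design warns of "under-representation of people with intellectual disabilities and co-occurring challenging behaviours in the dataset, as there may be a significant number of patients without a formal" (what they lack is a diagnosis). It also mentions inconsistent recording of behaviours, unrecorded physical conditions, and coding variation between practices and over time.

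**The concern.** A behaviour counts as an event only once it is coded. A physical condition also has to be coded, and having one may bring a patient to the practice more often. If so, existing behaviour has more chances to be recorded in patients with the condition than in those without it.

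This is not the general under-recording that the limitations describe. Under-recording that is equal in both groups mainly lowers the incidence or dilutes an association. Recording that differs by physical condition can create an association. It also acts between patients within one practice, so handling differences between practices or calendar periods does not remove it.

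Research question 2 asks whether physical conditions raise or lower the incidence of challenging behaviour. The study is labelled hypothesis testing and is meant to be a foundation for intervention development. As specified, the analysis cannot distinguish an effect of a condition from more frequent recording.

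**Working it through.** **1. The Protocol's own figures.** 3,020,680 + 13,285,111 = 16,305,791 patients. × 0.005 = 81,529 with intellectual disabilities. × 0.165 = 13,452 with challenging behaviours. Both counts reproduce. The second is a prevalence, not a number of incident events. The Protocol gives no onset rate, contact rate or coding probability, so everything in steps 3 to 6 rests on assumed inputs.

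**2. Is contact handled anywhere?**

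| Place in Protocol | What is handled | Contact measure |
|---|---|---|
| Phase 2, step (i), and Plan for addressing confounding | age, sex, ethnicity, deprivation | none |
| Phase 2, step (ii) | severity, autism, genetic syndromes, mental comorbidities | none |
| Definition of the study population | sensitivity analysis for leavers | none |
| Plans for addressing missing data | multiple imputation | none |
| Limitations of study design | general under-recording; practice and time variation | not mentioned |

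**3. Illustration with a true ratio of 1.0.** Assume that behaviour begins at rate λ = 0.02 per year in both groups. After onset it is coded at rate d = consultations per year × probability p of coding per consultation. Follow-up is T = 5 years. Then:

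- P(coded by T) = 1 − [d·exp(−λT) − λ·exp(−dT)] / (d − λ)
- person-years per patient = [d(1 − exp(−λT))/λ − λ(1 − exp(−dT))/d] / (d − λ)
- recorded rate = the first divided by the second

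For p = 0.05 and 4 consultations a year (d = 0.2): 0.0355 / 4.936 = 0.00719. For 8 a year (d = 0.4): 0.0547 / 4.895 = 0.01117. The ratio is 0.01117 / 0.00719 = 1.55.

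| p per consultation | 8 vs 4 a year | 6 vs 4 a year |
|---|---|---|
| 0.05 | 1.55 | 1.31 |
| 0.10 | 1.34 | 1.21 |
| 0.30 | 1.10 | 1.07 |

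**4. Range over 10 years.** The same formulas with T = 10, where d is the coding rate in the group with less contact:

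| d per year | contact × 1.25 | × 1.5 | × 2 |
|---|---|---|---|
| 0.05 | 1.21 | 1.40 | 1.74 |
| 0.2 | 1.12 | 1.21 | 1.35 |
| 0.5 | 1.05 | 1.09 | 1.13 |
| 2 | 1.01 | 1.02 | 1.03 |

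The bias is large when coding is sparse and almost nil when it is prompt.

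**5. Does sample size protect?** The chance that a ratio is declared significant (two-sided 5%, assumed) is Φ(√[D·a(1−a)]·ln HR − 1.96), with D events and a share a of patients with the condition. For a spurious ratio of 1.20 and D = 3,000 (assumed), it is 0.59, 0.85 and above 0.99 for a = 5%, 10% and 30%. If 13,452 were the event count, it would be above 0.99 in all three. A large cohort makes such a bias more likely to be declared significant.

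**6. Would adjustment help?** Using the model in step 3, contact was allowed to vary between patients (gamma, shape 2, assumed), with means of 8 and 4 a year. Adjusting for a six-month consultation count before follow-up cut the spurious ratio from 1.52 to 1.20 at p = 0.05, and from 1.34 to 1.14 at p = 0.10. The reduction is substantial but partial. With less variation between patients (shape 4) it is smaller: 1.51 to 1.27 and 1.34 to 1.19.

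**The case against.** The strongest reply is that the Protocol does not say patients with physical conditions consult more, and some listed conditions, such as sensory impairment, need not bring more consultations. Every input to the illustration is assumed, and with prompt coding the bias all but disappears. This stands: the point shows an open route to bias, not a demonstrated one.

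A reader might infer that the bias is upward for every condition that brings patients to the practice, or that any association found would be nothing but contact frequency. The documents do not support either reading. The first needs the same chance of coding at every consultation, whatever its reason. If visits for a physical complaint yield fewer behaviour codes, the bias shrinks or reverses. The second would need a known size. Nor does the Protocol say that a code arises only when a clinician sees the patient; it requires only that a code be recorded.

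It can also be said that the limitations already admit poor recording, and that step (ii) of Phase 2 adjusts for severity and mental comorbidities, which may drive contact. Both help only in part. The limitations do not mention recording that differs by physical condition, and those covariates enter as mediators and do not measure contact.

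Finally, an added sensitivity analysis could be left to a statistical analysis plan, which is not shown. That carries some weight, but the Protocol itself fixes the confounder list and names its sensitivity analyses, and contact is absent from both.

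**Conclusion.** The point holds as a gap in the planned analysis. Outcome and physical conditions both depend on recorded codes, and nothing in the models, sensitivity analyses or limitations deals with recording that differs by a patient's contact. The Cox models could therefore give a positive hazard ratio for a condition with no true effect.

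The conclusion depends on two things the Protocol does not establish: that patients with the condition have more contact, and that coding of existing behaviour is not prompt. Under the assumed inputs, the spurious ratio runs from about 1.0 to about 1.5 with doubled contact over 5 years, and to about 1.7 in the sparsest 10-year case. The direction is probably upward but is not assured for every condition. A sensitivity analysis and a fuller limitations statement are warranted; replacing the main model is not.

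**What to change.** Add to Phase 2 and to Plan for addressing confounding one pre-specified sensitivity analysis of the first-event Cox models:

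- Adjust for the patient's consultation count in a fixed window before the start of follow-up: at least six months of registration, longer where available.
- Limit it to patients with that look-back, and refit the main model in the same patients for comparison. The restriction is needed because Definition of the study population does not give everyone six months. The first inclusion criterion requires it before entry. The second does not say before what, and patients who register after 1 January 2009 are followed from registration.
- Report it beside the main model. State in the interpretation and in Limitations of study design how far each hazard ratio attenuates. Do not make it a condition for concluding that an association exists.

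Restricting person-time to patient-years with at least one consultation is not a substitute. At 4, 6 or 8 consultations a year (Poisson), 1 − exp(−4) = 98.2%, 1 − exp(−6) = 99.8% and 1 − exp(−8) = 99.97% of patient-years already qualify. Almost none of the bias would go, and the restriction selects on contact during follow-up, which the condition or the behaviour may affect.

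The cost is one derived count from the primary-care records and one extra set of models. The downsides are that contact is partly a result of the condition, so the adjusted estimate may be conservative, and that a short count is a noisy proxy that removes only part of the bias.

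### Physical-condition codes carry no date rule; used as a fixed 'ever recorded' covariate, the natural but unstated reading, they would leave research question 2 open to immortal-time or reverse-causation bias

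*Protocol*

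**What the plan says.** In Exposures, outcomes and covariates the variable is introduced as "Moderator: record of co-occurring physical conditions". Patients with pain, sleep problems, constipation, epilepsy, incontinence or sensory impairment "will be identified using searches for any relevant READ code, as has been done previously with CPRD". Neither that section, nor Outcomes to be measured, Definition of the study population, Phase 1 or Phase 2, dates the code against cohort entry or against the first challenging-behaviour record. None says how a condition first coded during follow-up is handled.

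Follow-up does have dates. Entry is 1 January 2009 at the earliest; otherwise, "Patients who register after 1/1/2009, or who are diagnosed with intellectual disabilities during the study period, will be followed from that date". Patients with earlier challenging behaviour are kept as cases, one index date being "1/1/2009 (if a patient is actively registered on this date with a diagnosis of challenging behaviours prior to 2009").

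On the model, Phase 2 states: "The main statistical analyses will be conducted using stratified Cox proportional hazard models". Time-varying terms appear in one place: "Where the assumption of proportional hazards is violated, we will augment the models with time varying covariates". A Poisson regression for repeated events follows, and Phase 1 stratifies incidence by physical condition, among other factors.

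The question to be answered is whether physical conditions "increase/decrease the incidence of challenging behaviours in primary care patients with intellectual disabilities".

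**The concern.** An effect on incidence requires the condition to be present before the behaviour. Some of the listed conditions can begin during follow-up, which runs up to 11 years (1 January 2009 to 31 December 2019). If such a condition is entered as a fixed yes/no from time zero, two things can go wrong, depending on which codes are counted.

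- **Codes up to event or censoring.** A patient coded in year 6 must have been free of challenging behaviour for six years to be classed as exposed. That event-free time is credited to the exposed group, which pulls the hazard ratio below 1.
- **Codes at any time.** A condition first recorded after challenging behaviour, perhaps through the consultations it prompts, is treated as if it came first. If recording rises after the outcome, the hazard ratio is pushed above 1.

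The two readings err in opposite directions, so an unstated programming choice could decide the sign of the answer to question 2. The stratified incidence and the Poisson rate ratios share the problem, because person-time before the code would be assigned to the exposed group.

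**Working it through.** **The plan's own figures.** Registered patients: 3,020,680 + 13,285,111 = 16,305,791. With 0.5% having intellectual disabilities: 16,305,791 × 0.005 = 81,528.96, stated as 81,529. With 16.5% having challenging behaviours: 81,529 × 0.165 = 13,452.3, stated as 13,452. Both reproduce. The protocol gives no hazard ratio, onset rate or prevalence for the physical conditions, so the size of any bias has to be explored under assumptions.

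**Set-up, with true hazard ratio 1.** One cohort of N = 81,529 per scenario and a maximum follow-up of 11 years.

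- Outcome rate: λ = −ln(1 − R)/11, with 11-year risk R of 5%, 16.5% or 30%. The 16.5% is the protocol's prevalence, used here as a cumulative risk; that use is an assumption. At 16.5%, λ = 0.1803/11 = 0.0164 per year.
- Condition: a proportion already coded at entry (10% or 5%). In the rest, onset is at rate μ = −ln(1 − P)/11, with P the 11-year probability of a first code (10%, 20% or 30%). At 20%, μ = 0.2231/11 = 0.0203 per year. Assumed.
- Leaving the practice: exponential with mean 12 years. Assumed.
- Model: Cox regression with one binary covariate, coded in five ways:
  - A: fixed, any code before event or censoring
  - B: fixed, any code until leaving the practice, recording unrelated to the outcome
  - C: as B, with the recording rate doubled after challenging behaviour
  - D: fixed, codes before entry only
  - E: time-updated from the first code

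**Estimated hazard ratios (truth 1.0)**

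| R | Coded at entry | P | A | B | C | D | E |
|---|---|---|---|---|---|---|---|
| 5% | 10% | 10% | 0.75 | 1.00 | 1.24 | 0.99 | 1.00 |
| 5% | 10% | 20% | 0.67 | 1.05 | 1.46 | 1.02 | 1.04 |
| 5% | 5% | 30% | 0.55 | 1.02 | 1.52 | 0.95 | 1.08 |
| 16.5% | 10% | 10% | 0.73 | 0.98 | 1.23 | 1.00 | 0.97 |
| 16.5% | 10% | 20% | 0.66 | 1.02 | 1.38 | 1.04 | 1.02 |
| 16.5% | 5% | 30% | 0.53 | 1.02 | 1.53 | 1.05 | 1.01 |
| 30% | 10% | 10% | 0.80 | 1.05 | 1.30 | 1.02 | 1.06 |
| 30% | 10% | 20% | 0.65 | 0.98 | 1.33 | 0.97 | 1.00 |
| 30% | 5% | 30% | 0.52 | 0.99 | 1.46 | 1.03 | 0.99 |

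Ranges: A 0.52–0.80; B 0.98–1.05; C 1.23–1.53; D 0.95–1.05; E 0.97–1.08. Each cell is a single run, and B, D and E scatter around 1 as expected from simulation noise. A is further from 1 when more of the exposed patients acquire the code during follow-up.

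**A case that needs no simulation.** A patient indexed at 1 January 2009 because challenging behaviour was recorded earlier already has the outcome. Any condition first coded after that date necessarily follows it, yet the code definition would count it.

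**The case against.** The strongest reply is that the protocol is silent rather than wrong. The code definition can be read as saying which codes qualify, not which dates. The sentence on time-varying covariates describes a remedy for non-proportionality and does not say that covariates are otherwise undated. The planned tables of baseline characteristics and the six-month registration rule are compatible with status being taken at entry, and on that reading (D), or with time-updating (E), there is no bias. Look-back windows and record splitting are also often left to a statistical analysis plan.

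Much of this stands. A reader might infer that bias is built in; the text does not support that, because the fixed covariate is an inference and the two mechanisms are alternatives. Even the broadest reading, codes at any time, gives about 1.0 unless recording changes after the outcome. A reader might also infer that the aim of learning "what the nature and direction of this association may be" cannot be met. Next to a question about increase or decrease, direction there plausibly means sign, not temporal order. Finally, Phase 2 names physical conditions only at the interaction step, so the main effect simulated here is implied by question 2 rather than written into the model.

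What does not stand is that this is only missing detail. The protocol sets an undated definition, makes time-varying terms conditional on a diagnostic for something else, and keeps patients whose outcome precedes entry as cases. An analysis plan that followed these words literally would carry the problem forward.

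**Conclusion.** The point holds as a weakness in how the exposure for question 2 is defined, not as proof that the analysis will be biased. Under the natural reading, a null association could appear as a hazard ratio of about 0.5 to 0.8 if codes up to event or censoring count, or about 1.2 to 1.5 if codes at any time count and recording doubles after challenging behaviour. It would stay near 1.0 if recording is unrelated to the outcome. These sizes rest on assumed onset, prevalence, leaving and recording rates, and on treating the 16.5% prevalence as an 11-year risk; they illustrate the scale and do not predict it. In a cohort of the size expected, a bias of this order could look like a precise finding. Conditions mostly recorded before entry would be less affected than those that begin during follow-up.

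**What to change.** State one dating rule for physical conditions and apply it to the Cox models, the Poisson models and the stratified incidence. Either:

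1. treat each condition as time-updated, unexposed from entry until its first code and exposed afterwards, ignoring codes dated after the first challenging-behaviour record in first-event analyses; or
2. use a fixed covariate based only on codes dated before cohort entry.

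Under either rule, state that patients whose challenging behaviour predates entry do not count as incident events in these analyses. Say also that time-updating of exposure does not depend on the proportional-hazards test.

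The first option costs record splitting at the code date. The second is simpler but leaves fewer exposed patients. Neither needs new data. A lagged analysis, in which exposure starts some time after the code to allow for same-visit recording, is an optional sensitivity analysis.
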